#### **4.13. Ethical considerations**

The ethical approval for the study will be sought from MUHAS Institutional Review Board, Tanzania and Tropical Diseases Research Control Institute (TDRC), Zambia. Permission to conduct the study shall be sought from District Education Board Secretaries (DEBS). Participation will be on voluntary bases and only adolescents whose parents will agree and sign informed written consent (Appendix 3 and 4). All treatment will be done according to Zambia dental standard treatment guidelines by qualified

registered dental personnel. Children in the control group who will be found with oral health problems will be attended and will receive the whole package of intervention at the end of the follow visit. Confidentiality of the information shall be maintained and freedom to withdraw and join the study at any time will be respected.

#### **4.14. Study limitation and mitigation**

##### **Study limitations**

1. The follow up duration will be limited to 24 months which is enough to observe change in oral health related behaviors, plaque and bleeding but not reasonably enough for observing dental caries increment.
2. The study will follow single blind design where only the examiners will be blinded, the principal investigator and the participants will not be blinded due to the nature of the intervention which requires administration of educational technical materials and provision of treatment which cannot be easily concealed.
3. Adolescents may modify their oral health related behavior in response to awareness that there are being observed (Hawthorne effects).

##### **Mitigation**

- 1 Dental caries assessment using CAST (Frencken *et al.*, 2011) will be used to capture incremental stages of dental caries development and dental caries variable will continue being followed up after 24 months.
- 2 The data analyst will be blinded during analysis stage to avoid subjective decisions on handling missing data, transforming variables, undertaking subgroup analysis, and selecting covariates due to prior knowledge of treatment allocation.
- 3 The interventions will end six months before the last follow up and therefore the effect of adolescents acting due to the reason that their being followed-up will be controlled in the data collected at the last follow up visit.

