### **2.2. Specific Objectives**

- 1 To determine prevalence and distribution of dental caries, periodontal conditions and oral impacts on daily performance among adolescents in Copperbelt Province, Zambia
- 2 To determine the association between dental caries and oral health related quality of life among adolescents in Copperbelt Province
- 3 To assess the effects of a six months modified basic package of oral care intervention on knowledge and behaviors related to dental caries after 18 and 24 months of follow up.
- 4 To assess the effects of a six months modified basic package of oral care intervention on prevalence of dental caries after 18 and 24 months of follow up
- 5 To assess the effects of a six months modified basic package of oral care intervention on prevalence of oral impacts on daily performance after 18 and 24 months of follow up

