|                                                                                                                                           |               | 2. OUT sessions 1-3                            | 1 st                                  |                 |                 |                 |                 | 2 nd |                 |                 | 3 rd | No OUT  |                  |
|                                                                                                                                           |               | 3. ART sessions 1-3                            | 1 st                                  |                 |                 |                 |                 | 2 nd |                 |                 | 3 rd | NO ART  |                  |
|                                                                                                                                           |               | 4. AFT sessions 1-9                            | 1 st                                  | 2 nd | 3 rd | 4 th | 5 th | 6 th | 7 th | 8 th | 9 th | -No AFT |                  |
|                                                                                                                                           |               | 5. Follow ups (at 3, 6, 12, 18, and 24 months) |                                                  |                 | 1 st |                 |                 | 2 nd |                 |                 | 3 rd |         | 4 th  |
|                                                                                                                                           | Control       | 1. Modified BPOC (OHE/OUT/ART/AFT) at the end  |                                                  |                 |                 |                 |                 |                 |                 |                 |                 |         | B
P
O
C |

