## Appendix 6- Analysis Plan by objectives

| No | Objective                                                                                                                                                                       | Analysis                                                                   | To be reported as                                              |
|----|---------------------------------------------------------------------------------------------------------------------------------------------------------------------------------|----------------------------------------------------------------------------|----------------------------------------------------------------|
| 1  | To determine prevalence and distribution of dental caries, periodontal conditions and oral impacts on daily performance among adolescents in Copperbelt Province, Zambia        | Frequency distribution, chi-square test, logistic regression               | Number and percentage, odds ratio with 95% confidence interval |
| 2  | To determine the association between dental caries and oral health related quality of life among adolescents in Copperbelt Province                                             | Frequency distribution, chi-square test, hierarchical logistic regression  | Number and percentage, odds ratio with 95% confidence interval |
| 3  | To assess the effects of a six months modified basic package of oral care intervention on knowledge and behaviors related to dental caries after 18 and 24 months of follow up. | Frequency distribution, chi-square test, generalized estimating estimation | Number and percentage, odds ratio with 95% confidence interval |
| 4  | To assess the effects of a six months modified basic package of oral care intervention on prevalence of dental caries after 6 and 12 months of follow up                        | Frequency distribution, chi-square test, generalized estimating estimation | Number and percentage, odds ratio with 95% confidence interval |
| 5  | To assess the effects of a six months modified basic package of oral care intervention on prevalence of oral impacts on daily performance after 18 and 24 months of follow up   | Frequency distribution, chi-square test, generalized estimating estimation | Number and percentage, odds ratio with 95% confidence interval |

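### The mitigation for too-short caries follow-up is not carried through: caries is analysed only as pupil-level prevalence, and follow-up after 24 months has no visit and no untreated control group

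*Protocol*

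**What the plan says.** Caries status is among the primary outcomes (section 4.10). The first limitation in section 4.14 says that 24 months is "not reasonably enough for observing dental caries increment". The matching mitigation is that CAST "will be used to capture incremental stages of dental caries development and dental caries variable will continue being followed up after 24 months".

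The caries effect is defined elsewhere. Objective 4 in section 2.2 is the effect on "prevalence of dental caries after 18 and 24 months of follow up". Appendix 6 row 4 has the same objective with other times, "prevalence of dental caries after 6 and 12 months of follow up", reported as number, percentage and odds ratio. Section 4.12 summarises caries experience as number and percentage and compares the arms by generalized estimating equations with odds ratios. The caries definition (key terms and section 4.9.2.5) starts at a visible enamel change.

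Section 4.9.1 calls the 24-month visit the last follow-up. Table 1 gives the control arm "Modified BPOC (OHE/OUT/ART/AFT) at the end", and section 4.13 says that control children found with problems "will receive the whole package of intervention at the end of the follow visit".

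**The concern.** The Protocol names a threat to a primary outcome and offers a two-part remedy, but the parts of the plan that would have to deliver it do not.

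First, CAST has ten codes, and the form in Appendix 2 charts them by surface on 28 teeth. The analysis reduces this to whether a pupil has caries. A pupil who is already a case cannot show a second lesion, or progression from enamel to dentine or pulp.

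Second, later follow-up cannot extend the package-versus-no-package comparison once controls are given the package, and no later visit exists in the schedule.

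At stake is how the caries result can be read. A null result could reflect no effect or an insensitive measure. If later data were collected, convergence of the arms might be mistaken for loss of effect.

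**Working it through.** **1. The plan's own figure.** Section 4.4: 2N = 4(1.96 + 1.03)² × 1.34² / 0.268² = 894.01. Design effect 1 + 79 × 0.01 = 1.79, and 894 × 1.79 = 1600.26. Then 1600 × 1.10 = 1760. The size reproduces. It rests on a difference in mean DMFT, which is a count, not on prevalence.

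**2. Remedy against plan.**
- Incremental stages (4.14): no code transition, ordinal score or increment appears in Objective 4, section 4.12 or Appendix 6.
- Follow-up after 24 months (4.14): no later visit appears in section 4.9.1, Table 1 or the activity plan, and controls receive the package at the end.

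**3. What prevalence means is not fixed.** If it is caries experience (the term in section 4.12), an affected pupil stays a case. If it is untreated caries, ART and extraction lower it mechanically in the intervention arm, where the treatment sessions are scheduled. Neither reading measures increment.

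**4. Pupils already cases.** Taking the African prevalence range in section 3.0 as an assumed baseline: 0.088 × 1600 = 141 and 0.5098 × 1600 = 816 pupils.

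**5. Illustration of power, on the caries-experience reading.**

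From the Protocol: 800 pupils per arm after losses and design effect 1.79, so 800 / 1.79 = 447 effective; two-sided 1.96; a 24% reduction (the fluoride-toothpaste figure for tooth surfaces in section 3.0, applied here to new lesions).

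Assumed: baseline mean b = 0.5 or 1.34 (the second is the Protocol's mean DMFT); control new lesions over 24 months i = 0.3, 0.5 or 0.8; gamma-Poisson variation between pupils with shape k = 0.5 or 1. This gives 12 scenarios.

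Formulas:
- Share of new lesions in pupils already affected: 1 − (1 + b/k)^−(k+1)
- Baseline prevalence: 1 − (1 + b/k)^−k; at follow-up, replace b by b + i (control) or b + 0.76i (intervention)
- Change in prevalence: follow-up minus baseline, that is, pupils with a first lesion
- Increment: mean i, variance i + i²/k
- Power: Φ(d/SE − 1.96) + Φ(−d/SE − 1.96), with SE = √[(v₁ + v₂)/447]

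Most favourable case (b = 0.5, k = 1, i = 0.8):
- Prevalence: 1 − 1/2.3 = 0.565 against 1 − 1/2.108 = 0.526; odds ratio 1.108/1.3 = 0.85; d/SE = 0.0396/0.0333 = 1.19; power 22%.
- Change in prevalence: baseline 0.333, so 0.232 against 0.192; d/SE = 0.0396/0.0273 = 1.45; power 31%.
- Increment: 0.800 against 0.608, variances 1.440 and 0.978; d/SE = 0.192/0.0736 = 2.61; power 74%.

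Over all 12 scenarios:

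| Quantity | Range |
|---|---|
| New lesions in pupils already affected | 56–86% |
| Prevalence odds ratio | 0.85–0.97 |
| Power, follow-up prevalence | 6–22% |
| Power, change in prevalence | 11–31% |
| Power, per-pupil increment | 39–74% |

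Simulation of the same model gives slightly wider ends, 10–31% for change in prevalence and 37–75% for increment. Those wider ranges are used in the conclusion.

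**6. Dependence on the effect.** Section 3.0 also cites brushing programmes that cut the proportion with caries by 24–50%. If that applied directly to prevalence, power at 447 per arm would be:

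| Control prevalence | 24% reduction | 50% reduction |
|---|---|---|
| 8.8% | 22% | 76% |
| 30% | 69% | about 100% |
| 50.98% | 96% | about 100% |

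**The case against.** - **CAST still helps.** A case threshold at enamel change registers first lesions earlier than a cavitation threshold would. This stands: a reader might infer that CAST adds nothing or that the mitigation cannot work at all, and the Protocol does not support that. What is lost is progression and further lesions in affected pupils.
- **An affected pupil need not stay a case.** The definition does not say how restored or extracted teeth count, so permanence holds only on the caries-experience reading. This stands, but the other reading confounds treatment with prevention.
- **The low prevalence power depends on the effect chosen.** Step 6 bears this out. Analysing change from baseline, in line with the paired analysis in section 4.9.1, also narrows the gap, though increment remains ahead in every scenario.
- **Randomisation survives 24 months.** One might infer that later data are no longer a randomised comparison. They are, but of early with delayed package. Section 4.13 could also be read as limiting the late package to controls with problems; Table 1 has no such limit. No later analysis is planned, so the risk of misreading is prospective.
- **Scoring can be left to an analysis plan, and section 4.12 lists means (SD).** This is fair for scoring detail. But the Protocol itself fixes prevalence and the odds ratio as the caries effect.
- **Increment is what the Protocol says 24 months cannot show well.** True, and its power also falls short of 85%. It is the more sensitive use of the same examinations, not a full rescue.

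**Conclusion.** The mitigation in section 4.14 is not carried through. Stage information is collected but not analysed, and the extended follow-up has neither a visit nor an untreated comparator. Under the stated assumptions, power is about 6–22% for follow-up prevalence, 10–31% for change in prevalence and 37–75% for per-pupil increment. All are below the planned 85%, and a larger effect would raise them. The lesion rates and dispersion are assumptions; the ordering of the three measures held in all 12 scenarios. The 6- and 12-month times in Appendix 6 row 4, if they applied, would make the conceded limitation worse. This should be fixed. It is not fatal, since the Protocol discloses the limitation and the needed data are already to be collected.

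**What to change.** 1. **Objective 4 and Appendix 6 row 4** ("To assess the effects of a six months modified basic package of oral care intervention on prevalence of dental caries"): add, as the main between-arm caries analysis, a per-pupil CAST increment and progression count from the paired surface charts within the randomised 24 months. Analyse it by cluster-adjusted GEE and report a rate ratio. Keep prevalence as a supporting measure and state whether it means caries experience or untreated caries.
2. **Define the count so that treatment given by the trial creates no events.** A surface counts by its last carious code before restoration or extraction, and sound surfaces of an extracted tooth are not new lesions. Otherwise extractions, scheduled as study sessions only in the intervention arm until the end, would bias the count against that arm.
3. **Reconcile the time points**: 18 and 24 months in Objective 4, 6 and 12 months in Appendix 6 row 4.
4. **Section 4.14**: remove follow-up after 24 months as a mitigation, or label it an early-versus-delayed comparison.

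The cost is wording and an analysis of charts already planned. The downsides are a less familiar effect measure and power that, on the assumptions above, still falls short of 85%.

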#### **4.15. Dissemination of findings**

Dissemination of findings will be done by presentations at regional and international conferences. The study is also expected to produce the following manuscripts for publication in local and international journals;

1. Socio-demographic and behavioral correlates of oral health among early adolescents in Copperbelt province, Zambia.
2. Impact of oral diseases on daily performance of adolescents in Copperbelt province, Zambia.
3. Impact of modified WHO –BPOC intervention on oral health and OHRQL among adolescents in Copperbelt province, Zambia.
4. Impact of modified WHO – BPOC intervention on reducing oral health disparities among adolescents in Copperbelt province, Zambia.

## 5.0. Budget

| ITEM DESCRIPTION AND REQUIREMENTS             | Unit              | Quantity | Unit cost (TSh) | Total cost (TSh)    |
|-----------------------------------------------|-------------------|----------|-----------------|---------------------|
| A. Stationery and secretarial services |                   |          |                 |                     |
| A4 sheets of papers                           | rim               | 5        | 10,600.00       | 53,000.00           |
| Ball pens                                     | dozen             | 2        | 5,000.00        | 10,000.00           |
| Pencils                                       | dozen             | 1        | 900.00          | 900.00              |
| Note books                                    | each              | 10       | 6,000.00        | 60,000.00           |
| Printing of proposal                          | Copies            | 1        | 9,000.00        | 9,000.00            |
| Photocopying of proposal                      | Copies            | 6        | 3,000.00        | 18,000.00           |
| Binding of proposal                           | Copies            | 6        | 2,000.00        | 12,000.00           |
| Consent form photocopying                     | Per page          | 1000     | 100.00          | 100,000.00          |
| Questionnaire photocopying                    | Per page          | 5000     | 100.00          | 500,000.00          |
| Photocopying of OHE materials                 | Each              | 120      | 100.00          | 12,000.00           |
| Printing of thesis                            | Copies            | 1        | 12,000.00       | 12,000.00           |
| Photocopying of thesis                        | Copies            | 4        | 3,000.00        | 12,000.00           |
| Loose binding of thesis                       | Copies            | 4        | 2,000.00        | 8,000.00            |
| Final binding of thesis                       | Copies            | 8        | 12,000.00       | 96,000.00           |
| Subtotal                               |                   |          |                 | 902,900.00   |
|                                               |                   |          |                 |                     |
| B. Personnel costs                     |                   |          |                 |                     |
| Allowance to 3 researchers                    | Days              | 90       | 60,000.00       | 5,400,000.00        |
| Allowance to 2 assistants                     | Days              | 90       | 20,000.00       | 1,800,000.00        |
| Incentives to teachers                        | Each              | 12       | 10,000.00       | 120,000.00          |
| Sub total                              |                   |          |                 | 7,320,000.00 |
|                                               |                   |          |                 |                     |
| C. Transport and communication         |                   |          |                 |                     |
| Fuel costs (baseline data)                    | Liters            | 360      | 2,660.00        | 957,600.00          |
| Transport Dar es Salaam to Ndola              | Return air ticket | 2        | 920,000.00      | 1,840,000.00        |
| Internet and telephone                        | Voucher           | 50       | 5,000.00        | 250,000.00          |
| Sub total                              |                   |          |                 | 3,047,600.00 |
|                                               |                   |          |                 |                     |

| ITEM DESCRIPTION AND REQUIREMENTS                    | Unit    | Quantity | Unit cost (TSh) | Total cost (TSh)     |
|------------------------------------------------------|---------|----------|-----------------|----------------------|
| D. Dental instruments, materials and supplies |         |          |                 |                      |
| Fuji IX                                              | Each    | 12       | 150,000.00      | 1,800,000.00         |
| Zinc oxide eugenol                                   | Each    | 9        | 80,000.00       | 720,000.00           |
| Lignocaine 2%                                        | P/50    | 8        | 110,000.00      | 880,000.00           |
| Cotton wool                                          | 500g    | 4        | 15,000.00       | 60,000.00            |
| Methylated spirit                                    | 5litres | 3        | 18,000.00       | 54,000.00            |
| Sodium hypochlorite                                  | 5litres | 12       | 8,000.00        | 96,000.00            |
| Disposable cups                                      | P/100   | 12       | 22,600.00       | 271,200.00           |
| Paper towels                                         | P/100   | 12       | 15,000.00       | 180,000.00           |
| Calcium hydroxide                                    | set     | 6        | 90,000.00       | 540,000.00           |
| Tooth pastes 250mg                                   | dozen   | 570      | 11,500.00       | 6,555,000.00         |
| Tooth brushes                                        | dozen   | 380      | 3,560.00        | 1,352,800.00         |
| Examination set                                      | set     | 50       | 60,000.00       | 3,000,000.00         |
| Sub total                                     |         |          |                 | 15,509,000.00 |
|                                                      |         |          |                 |                      |
| E. Data Processing                            |         |          |                 |                      |
| Data entry                                           | days    | 20       | 20,000.00       | 200,000.00           |
| Data analysis                                        | days    | 5        | 100,000.00      | 500,000.00           |
| Sub total                                     |         |          |                 | 700,000.00    |
|                                                      |         |          |                 |                      |
| F. Dissemination                              |         |          |                 |                      |
| Attendance to local conferences                      | each    | 2        | 300,000.00      | 600,000.00           |
| Attendance to international conferences              | each    | 1        | 1,500,000.00    | 1,500,000.00         |
| Publication costs                                    | each    | 5        | 200,000.00      | 1,000,000.00         |
| Sub total                                     |         |          |                 | 3,100,000.00  |
|                                                      |         |          |                 |                      |
| G. Other costs                                |         |          |                 |                      |
| Ethical clearance MUHAS - Tanzania                   | each    | 1        | 300,000.00      | 300,000.00           |
| Ethical clearance TDRC - Zambia                      | each    | 1        | 460,000.00      | 460,000.00           |
| Subtotal                                      |         |          |                 | 760,000.00    |
| H. Incidental                                 | 10%     |          |                 | 3,121,950.00  |
| GRAND TOTAL                                   |         |          |                 | 34,341,450.00 |

